# Evidence-based Shared-Decision-Making Assistant (SDM-assistant) for choosing antipsychotics: protocol of a cluster-randomized trial in hospitalized patients with schizophrenia

**DOI:** 10.1186/s12888-022-04036-5

**Published:** 2022-06-17

**Keywords:** Health service research, SDM, EBM, Decision aid, Patient preference, Inpatient psychiatry, Psychosis, Antipsychotic, Response, Side-effect

## Abstract

**Background:**

Choosing an antipsychotic medication is an important medical decision in the treatment of schizophrenia. This decision requires risk-benefit assessments of antipsychotics, and thus, shared-decision making between physician and patients is strongly encouraged. Although the efficacy and side-effect profiles of antipsychotics are well-established, there is no clear framework for the communication of the evidence between physicians and patients. For this reason, we developed an evidence-based shared-decision making assistant (SDM-assistant) that presents high-quality evidence from network meta-analysis on the efficacy and side-effect profile of antipsychotics and can be used as a basis for shared-decision making between physicians and patients when selecting antipsychotic medications.

**Methods:**

The planned matched-pair cluster-randomised trial will be conducted in acute psychiatric wards (*n* = 14 wards planned) and will include adult inpatients with schizophrenia or schizophrenia-like disorders (*N* = 252 participants planned). On the intervention wards, patients and their treating physicians will use the SDM-assistant, whenever a decision on choosing an antipsychotic is warranted. On the control wards, antipsychotics will be chosen according to treatment-as-usual. The primary outcome will be patients’ perceived involvement in the decision-making during the inpatient stay as measured with the SDM-Q-9. We will also assess therapeutic alliance, symptom severity, side-effects, treatment satisfaction, adherence, quality of life, functioning and rehospitalizations as secondary outcomes. Outcomes could be analysed at discharge and at follow-up after three months from discharge. The analysis will be conducted per-protocol using mixed-effects linear regression models for continuous outcomes and logistic regression models using generalised estimating equations for dichotomous outcomes. Barriers and facilitators in the implementation of the intervention will also be examined using a qualitative content analysis.

**Discussion:**

This is the first trial to examine a decision assistant specifically designed to facilitate shared-decision making for choosing antipsychotic medications, i.e., SDM-assistant, in acutely ill inpatients with schizophrenia. If the intervention can be successfully implemented, SDM-assistant could advance evidence-based medicine in schizophrenia by putting medical evidence on antipsychotics into the context of patient preferences and values. This could subsequently lead to a higher involvement of the patients in decision-making and better therapy decisions.

**Trial registration:**

German Clinical Trials Register (ID: DRKS00027316, registration date 26.01.2022).

**Supplementary Information:**

The online version contains supplementary material available at 10.1186/s12888-022-04036-5.

## Background

A large number of antipsychotics are available for the treatment of schizophrenia with substantial differences in their side-effect profiles and smaller in efficacy [1]. This makes the selection of an antipsychotic for the individual more difficult, given also that several factors should be taken into consideration, such as patient preferences, prior experiences, side-effect profiles, comorbidities, age and sex [2–5]. This “preference-sensitive” decision requires shared-decision-making (SDM) between patients and their treating physicians [4, 6]. In addition, physician decision-making behaviours are often not evidence-based, but influenced by irrational factors [7–9], cognitive biases [10, 11], and lack of statistical knowledge [12]. Furthermore, decisions in the treatment of schizophrenia are perceived by many patients as “paternalistic” or dominated by the physician, without patients really having a choice about which drug to be prescribed [13, 14]. These aspects could lead to less optimised drug selection, poor therapeutic relationship, lower adherence and increased relapse rates [15].

In order to overcome the above defects in decision-making, we developed an evidence-based shared-decision-making assistant (SDM-assistant) for choosing antipsychotics. This newly developed tool provides a framework of shared-decision-making illustrating evidence from a network meta-analysis on the efficacy and side-effects of antipsychotics [1]. It may also overcome limitations of previous tools with limited capabilities in shared-decision-making or presenting evidence of lower quality [16]. Patients and practitioners can use the SDM-assistant as a basis of share-decision-making by discussing and navigating differences of antipsychotics. This could facilitate “better” therapy decisions (e.g., fewer adverse events) and increase patient involvement, and thus, could subsequently lead to greater patient satisfaction and, potentially, fewer rehospitalisations due to improved adherence [17, 18]. Figure 1 shows the potential outcomes of using the SDM-assistant for choosing antipsychotics, as adapted by our previous work on shared-decision making in patients with an acute exacerbation of schizophrenia [19].

**Fig. 1 Fig1:**
[figure not shown]
Potential outcomes of SDM-assistant for choosing antipsychotics

The planned cluster-randomized-controlled trial aims to compare the effects of SDM-assistant versus treatment-as-usual (TAU) in inpatients with schizophrenia. We will investigate whether the SDM-assistant can improve perceived shared-decision-making, lead to fewer side-effects and better adherence at discharge and three-months after discharge. We will also explore factors that could have an impact on the use and effects of the SDM-assistant tool.

## Methods

### Trial design

The planned study is a cluster-randomized-controlled trial evaluating the use of an evidence-based shared-decision making assistant (SDM-assistant) for choosing antipsychotics in patients with schizophrenia hospitalised in acute psychiatric wards in three hospitals in Munich, Germany (Klinikum rechts der Isar of the Technical University of Munich, Isar-Amper-Klinikum München-Ost and München-Schwabing). The protocol is registered in the German Clinical Trials Register (ID: DRKS00027316, registration date 26.01.2022). The protocol is reported according the SPIRIT [20] and SUNDAE [21] statements.

### Participants

Participants should have a diagnosis of a schizophrenia spectrum disorder (ICD-10 F20-F9) and be hospitalized in an acute psychiatric ward at the time of examination. They should be aged between 18 and 65 years at the time of inclusion and be able to give their informed consent to participate in the study. There are no other exclusion criteria, e.g., in terms of sex, ethnicity, illness stage.

### Intervention and control group

Antipsychotic drugs are recommended for the treatment of acute episodes of schizophrenia [4]. Therefore, decisions on choosing which antipsychotic drug to be used are necessary in acute psychiatric wards. In the intervention group, whenever a decision on choosing an antipsychotic is warranted (e.g., initiation, continuation or change of antipsychotic drugs), patients and their treating physicians will use the SDM-assistant in the context of a shared-decision-making process for the selection of an antipsychotic, in addition to the usual care. The SDM-assistant can be used more than once in different sessions during the trial. In the control group, patients and their treating physicians will not use the SDM-assistant, and antipsychotics will be chosen according to treatment-as-usual (TAU). Changes in the treating physicians will be discouraged, yet, when necessary, they will be recorded. In addition, we will use cluster randomization at the ward level, and therefore, a possible switch to a physician from the other arm of the trial would be unlikely. We will consider as protocol violations when patients do not receive at least one session of the SDM-assistant or when patients switch from the control to the intervention group or vice versa.

### SDM-assistant for choosing antipsychotics

The SDM-assistant is a browser-based-application developed by our team in accordance to the IPDASi v4.0 [22] (eAppendix 1) and provides an interactive framework of shared-decision-making between patients and physicians for the selection of antipsychotics. The SDM-assistant provides a basis for a decision; the final decision of the selection of the drug will be taken in a shared-decision-making process between clinician and patients, and there is no direct treatment recommendation provided by the SDM-assistant tool. Here, reference is made to the three-talk model of SDM, and the work with the decision aid is located in the “option talk” [23]. We included patients and relatives in the development and design of the SDM-assistant, and its final format and way of presenting the data was determined in pre-tests and focus groups.

Each session of the SDM-assistant is multi-step (Fig. 2). At the very beginning, treating physicians will receive training in the use of the SDM-assistant and will be introduced in the methods of evidence-based-medicine and shared-decision-making. In a first step, users (patients and physicians) work on the SDM-assistant separately. Patients get information from text descriptions and video presentations by health practitioners and ex-users about schizophrenia, aspects of drug treatment with antipsychotics, and shared-decision-making. Patients are then guided to think about their own goals and preferences for the treatment with antipsychotics (e.g., prior experience with antipsychotics, side-effects to avoid, antipsychotic formulation). Physicians, on the other side, enter clinically relevant patient information (e.g., age, sex, duration of illness, comorbidities).

**Fig. 2 Fig2:**
[figure not shown]
Session of SDM-assistant

In a second step, patients and physicians can jointly consult forest plots presenting evidence on antipsychotics (Fig. 3), and subsequently make a shared treatment decision.

**Fig. 3 Fig3:**
[figure not shown]
Forest plot interface of the SDM-assistant for choosing antipsychotics. Forest plots presenting effect-sizes (point estimates and their 95% credible intervals) for the comparisons of antipsychotics with placebo. Relative risks are used as the effect-size, except for mean differences in kg for weight gain. The figure was taken as a screenshot from the SDM-assistant for choosing antipsychotics

In the context of the study, evidence on twelve antipsychotics (i.e., amisulpride, aripiprazole, cariprazine, clozapine, haloperidol, olanzapine, paliperidone, perphenazine, quetiapine, risperidone, sertindole, and ziprasidone) licensed and commonly used in Germany is considered. Other antipsychotics were not considered, e.g. not yet licensed (e.g., brexpiprazole or lurasidone), old and not widely used (e.g., many first-generation antipsychotics) [24] and/or based on limited evidence from RCTs (e.g., fluphenazine or sulpiride) [1]. Published evidence from a large network meta-analysis conducted by our group is used [1]. Network meta-analysis is considered the highest level of evidence in treatment guidelines [25], and thus, can be informative for the shared-decision-making process. Both efficacy and side-effects are important for the selection of an antipsychotic [2, 3], therefore, we consider overall efficacy (reduction of overall symptoms as measured by validated scales) and six important side-effects of antipsychotics, i.e., weight gain, use of antiparkinsonian medications as a proxy of extrapyramidal symptoms, akathisia, sedation, anticholinergic side-effects (e.g., blurred vision, constipation, dry mouth or hyposalivation and urinary retention), and hyperprolactinaemia that could also be used a weak proxy of sexual side-effects [26, 27].

Forest plots present effect-sizes and their 95% credible intervals of the comparisons between antipsychotics and placebo. Relative risks are used as the effect-size in the forest plots, since they can be more intuitive than other measures such as odds ratios, standardized-mean-differences, or even mean-differences (e.g., in scale scores for overall efficacy and extrapyramidal symptoms or ng/ml for prolactin levels) [28]. However, mean-differences are presented for weight gain (in kg) because of their straightforward understanding for this outcome. When relative risks are not originally reported in the network meta-analysis [1], they are converted from other effect-sizes indices [29] (eAppendix 2). We prefer relative over absolute measures (e.g., absolute risk of a patient to have a side-effect) because they are generally constant across different baseline risks and definitions of the outcome [30], which are common in meta-analysis, especially for the side-effects of antipsychotics [31]. In addition, absolute measures require a baseline risk that can be difficult to be estimated for the individual. Nevertheless, the risk in the placebo group can be presented and discussed, i.e., the weighted percentage of patients in the placebo group with a positive response to treatment or a side-effect.

Patients and their physicians see first the forest plot of efficacy, in which antipsychotics are ranked from the best to the worst efficacy according to the ranking in the network meta-analysis [1]. Then, they can add or remove forest plots for the different side-effects. In that way, they can simultaneously look at effect-sizes of antipsychotics across different outcomes and change the ranking of antipsychotics based on one of these outcomes. They can remove antipsychotics from the list and provide reasons for exclusion. In the end of this step, patients and physicians select one (or more) antipsychotics as potential candidates to be used.

In order to facilitate the process, there are help buttons. In addition, there are short text descriptions for each outcome, and short summaries for each antipsychotic based on the findings of the network meta-analysis [1], treatment guidelines [4], reference textbooks [32] and the respective product leaflets (Fig. 4). The short summaries for each antipsychotic consist of a text description that provides information about the unique indications, contraindications, dosing, pharmacokinetics, and side-effect profile of the selected antipsychotic (also considering side-effects not presented in the forest plots, such as QTc prolongation, myocarditis and agranulocytosis etc.), and a plot that illustrates the relationship of the relative risk of the antipsychotic in comparison to the average relative risk of all antipsychotics with z-scores (eAppendix 2).

**Fig. 4 Fig4:**
[figure not shown]
Summary description and summary plot for amisulpride. The short summary for each antipsychotic (e.g., amisulpride) consists of a text description and a plot that presents Z-scores of relative risks across outcomes, which can show the relationship of the relative risk of amisulpride in comparison to the average relative risk of all medications. The figure was taken as a screenshot from the SDM-assistant for choosing antipsychotics

In a third step, patients and their physicians look at an overview of patient’s goals and preferences, clinically relevant patient characteristics, selected and excluded antipsychotic medications. They have the chance to further discuss and modify their selections.

In a fourth step, they finalize the antipsychotic selection and save the session.

### Outcomes

Recruitment and data collection will take place at the participating wards. Baseline data will be measured at inclusion and before using the SDM-assistant (T0). Then, the aim is that patients and physicians will use the SDM-assistant at least once during inpatient stay whenever a decision on choosing an antipsychotic is warranted, but no later than three weeks after admission. Both will also be encouraged to use the SDM-assistant as often as possible. At the time of discharge from the hospital, outcomes will be measured (T1). Three months after the discharge, we will contact each patient and the treating outpatient psychiatrist via telephone and/or post in order to obtain follow-up outcome data (T2). Table 1 presents a schematic diagram of participant timeline and data collection. Scales (German versions) could be filled accordingly by patients, their treating physicians or the study personnel (e.g., clinical psychologists not involved in the treatment of the patients and trained to administer the scales). Physicians and study personnel will receive training on the use of individual scales.

**Table 1 Tab1:**
[figure not shown]
Planned timepoints and data collection

#### Baseline parameters

We will record at baseline (T0) socio-demographics (i.e., age, sex, nationality, language, education, family and occupation status, digital literacy), anamnesis (ICD-10 diagnoses, duration of illness, number of previous hospitalizations, previously prescribed medications), and information about the current admission (legal status, voluntary or involuntary treatment with antipsychotics).

We will also record patient-related factors that could influence the shared-decision making for selecting treatments, i.e. patients’ participation preferences for decision making using the corresponding subscale of the Autonomy Preference Index [33], insight and perceived necessity of treatment using the Birchwood Insight Scale [34] and perception of the current admission using the MacArthur Admission Experience Survey [35].

#### Primary outcome

The primary outcome will be patients’ perceived involvement in decision-making using the Shared-Decision-Making Questionnaire (SDM-Q-9) [36] at T1. The SDM-Q-9 is a self-report scale consisting of nine items that describe different parts of the SDM process and reflecting the inpatient decision-making, e.g., here on the selection of antipsychotic medication. Each item will be scored from 0 “completely disagree” to 5 “completely agree”, and a total score will be calculated ranging from 0 to 45, with a higher score indicated a better-perceived involvement [36]. We expect that the use of the SDM-assistant would substantially improve patients’ perceived involvement, thus identifying a clinically meaningful mean difference of at least 15 points in SDM-Q-9 between the intervention and control group [37, 38].

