### Sample size and recruitment

The target sample size is *N* = 252 patients from *n* = 14 clusters (126 participants from 7 intervention wards and 126 participants from 7 control wards). Power calculation estimated *N* = 180 participants (*n* = 12 clusters) to be analysed in order to detect an expected Cohen’s d of 0.45–0.5 in the primary outcome of SDM-Q-9 with a power of at least 80% at two-sided alpha of 0.05 assuming ICC = 0.02. These assumptions are based on data from a comparable study (SDM-PLUS), which involved a similar population and the same main outcome parameter [38]. Due to an assumed drop-out rate of patients of 15–25% and to account for a potential drop out of clusters, we aim at recruiting *n* = 14 clusters and *N* = 252 patients.

Patient recruitment will be conducted by a trained study staff and will take place on the 14 selected wards at three hospitals in Munich, Germany (Klinikum rechts der Isar of the Technical University of Munich, kbo-Isar-Amper-Klinikum München-Ost and München-Schwabing). These hospitals with more than 1500 beds in total can facilitate the enrolment of the planned number of patients (*N* = 252) in a timely manner, as in our previous trials [38, 54].

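### The expected 15-point difference on a 0–45 SDM-Q-9 score is arithmetically incompatible with the expected Cohen's d of 0.45–0.5 used to size the trial

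*Protocol article*

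**What the plan says.** The Primary outcome section of the protocol article defines the SDM-Q-9 at discharge as nine items scored 0 to 5, for which "a total score will be calculated ranging from 0 to 45". The same section says the authors expect a substantial improvement amounting to a "clinically meaningful mean difference of at least 15 points in SDM-Q-9 between the intervention and control group", and cites references 37 and 38.

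The Sample size and recruitment section expresses the target differently. It aims to "detect an expected Cohen’s d of 0.45–0.5 in the primary outcome of SDM-Q-9". The other inputs there are power of 80% or more, a two-sided 5% significance level and an intracluster correlation of 0.02. The result is: "Power calculation estimated *N* = 180 participants (*n* = 12 clusters) to be analysed". These assumptions are attributed to a comparable study in a similar population with the same main outcome, which is reference 38 again.

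The Data analysis section makes the raw mean difference with its 95% confidence interval the effect measure for continuous outcomes. The article gives no standard deviation for the SDM-Q-9, mentions no rescaling, and does not connect the 15 points to d.

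**The concern.** A raw difference and a standardised difference for the same outcome are tied together by the standard deviation: d = difference / SD. Two of these determine the third, and here the third is a value that the stated scale does not allow. At least one of three statements must therefore be wrong or incomplete: the 15 points, the d, or the 0–45 metric to which the 15 points are taken to belong.

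What is at stake is how the primary result is read. It will appear as a mean difference in points, and the only points benchmark in the article is 15. A result equal to the effect the trial was built to detect would look disappointing against that benchmark. If the benchmark is corrected only after the results are known, in an open trial with a self-reported primary outcome, the correction could look like a lowering of the bar.

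**Working it through.** **Inputs.** From Primary outcome: score range 0–45 and a difference of 15 points. From Sample size and recruitment: d = 0.45–0.5, 180 analysed patients in 12 wards, power 80%, two-sided alpha 0.05, ICC 0.02, equal allocation ("126 participants from 7 intervention wards and 126 participants from 7 control wards" at recruitment). No SD is given, and steps 1 to 4 need none.

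**Step 1: reproduce the plan's own figure.** Patients per ward = 180/12 = 15. Design effect = 1 + (15 − 1) × 0.02 = 1.28. Total N = 2 × [2 × (1.960 + 0.842)² / d²] × 1.28.

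- d = 0.45: N ≈ 198
- d = 0.475: N ≈ 178
- d = 0.50: N ≈ 161

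The stated 180 falls inside this range, at d ≈ 0.47. So d has its usual meaning (difference divided by the individual-level SD), and the sample size was derived from d, not from 15 points.

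**Step 2: the SD that would reconcile the two figures.** SD = 15/d.

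- 15/0.50 = 30.0
- 15/0.45 = 33.3

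**Step 3: the largest SD the scale allows.** A score bounded by 0 and 45 with mean μ has variance of at most μ(45 − μ). This is largest at μ = 22.5, so the SD cannot exceed 22.5. If the two arm means differ by D, the largest pooled within-arm variance is (45² − D²)/4. With D = 15 this is (2025 − 225)/4 = 450, so the SD is at most 21.2. Both limits are far below 30.

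**Step 4: what each figure implies for the other.**

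- Smallest d compatible with 15 points: 15/22.5 = 0.67 on the simple bound, 15/21.2 = 0.71 on the sharper one.
- Largest raw difference compatible with d: solving D = d × √[(45² − D²)/4] gives D = 45d/√(4 + d²). That is 9.9 points at d = 0.45 and 10.9 points at d = 0.50. The simple bound gives 0.45 × 22.5 = 10.1 and 0.50 × 22.5 = 11.25.

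**Step 5: illustration at assumed SDs.** These SDs are not in the article and serve only to show the range.

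| Assumed SD | d implied by 15 points | Points implied by d = 0.45–0.5 |
|---|---|---|
| 8 | 1.88 | 3.6–4.0 |
| 10 | 1.50 | 4.5–5.0 |
| 15 | 1.00 | 6.75–7.5 |
| 20 | 0.75 | 9.0–10.0 |

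**Step 6: a possible explanation.** If the 15 points were on a score rescaled to 0–100, the raw equivalent would be 15 × 45/100 = 6.75 points. The linking SD would then be 6.75/0.50 = 13.5 to 6.75/0.45 = 15 on the 0–45 score, which is possible. The figures would then fit, but the article describes no such rescaling.

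**The case against.** The best defence is that a trial may be powered for an effect smaller than the one its authors hope for or regard as meaningful. On that view, 15 points and d = 0.45–0.5 answer different questions and need not agree. In principle this is right. The article does not say it, however. Both figures are presented as what is expected for the same outcome, both draw on the same comparable study, and nothing describes d as a cautious choice set below the meaningful difference.

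Three stronger readings are tempting and are not supported:

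- **That the sample size is wrong.** It is not invalidated by this conflict. It rests on d, ICC, alpha and power, and it reproduces in step 1. A true difference of 15 raw points would leave the trial overpowered: even at the largest possible SD of 21.2, power with 180 patients and design effect 1.28 is about 99% on a normal approximation.
- **That a result at the powered effect must be declared a failure.** A reader might infer this from the words describing the 15 points as clinically meaningful. But the Data analysis section sets no such rule. It plans a mean difference, a confidence interval and a two-sided 5% test, and never refers to 15 points.
- **That the 15 points are known to be on a 0–100 scale, or are known to exceed the powered effect by a particular multiple.** The first is a conjecture that happens to fit. The second depends on an SD that the article does not give.

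Nor is this a detail left to a fuller document: two stated figures conflict.

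**Conclusion.** The inconsistency is real, and it is established from the article's own figures without any assumed SD. On the 0–45 total as defined, 15 points corresponds to d of at least about 0.7, and d = 0.45–0.5 to at most about 10–11 points. No data set can satisfy both statements.

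The consequence is limited to the stated target and its interpretation. Type I error, power for the stated d and the planned model are untouched. A trial that finds exactly what it was powered for would nevertheless report a raw difference below the only difference the protocol calls clinically meaningful. How far below depends on the unknown SD: the shortfall is at least about 4 points (15 − 10.9), and more at any SD below the theoretical maximum.

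**What to change.** Before the analysis, reconcile the Primary outcome and Sample size and recruitment sections:

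1. State the expected difference on the 0–45 score that will be analysed, with the SD that links it to d = 0.45–0.5 and the source of that SD.
2. If the 15 points refer to a 0–100 rescaled score, say so and give the raw equivalent of 6.75 points (SD 13.5–15). If they do not, correct or remove the figure.
3. If a larger clinically meaningful difference is kept on purpose, say that it is not the difference the trial is powered to detect.

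The cost is a sentence or two in each section. Recruitment, conduct, sample size and the analysis model do not change. Making the correction before results are known keeps it from looking like a response to them.
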